### Trial design

2.1

This prospective study was conducted using a parallel-group design with two groups. In the experimental group, the optimized communication protocol was applied (OPT), whereas the standard-of-care group (SOC) received communication according to a control protocol that uses standard communication observed in the clinic with no particular consideration of the effects of communication. The required sample size for the planned analysis of the main outcome (i.e., complete datasets from t1 to t5) was N = 80 inpatients, recruited in the general wards of the Neurology Department at the University Hospital Essen, with a balanced 1:1 group allocation ratio (n = 40 for SOC, n = 40 for OPT). The study was preregistered at the German Clinical Trials Register (DRKS00032272). This study protocol aligns with the SPIRIT guidelines (Standard Protocol Items: Recommendations for Interventional Trials) and follows the SPIRIT-PRO extension for patient-reported outcomes, as specified in Supplementary Table S1 (Chan et al., 2013; Calvert et al., 2018).

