### Criteria for discontinuing study participation

2.5

Study participation was to be terminated preemptively if the following occurred after enrollment: LP no longer indicated by medical personnel or the patient declined or aborted the procedure; failed attempt at lumbar puncture with no collection of CSF; patient retroactively withdrew consent for study participation or for use of the data; other medical or logistical barriers to study continuation on the part of the patient (e.g., discharge before the LP, significant deterioration in health, extended unavailability or incompliance of the patient for study participation) or the study personnel (e.g., unplanned unavailability of study personnel without adequate replacement or feasibility of rescheduling the lumbar puncture); later emergence of exclusion criteria (i.e., change in LP indication to a therapeutic CSF drainage). Patients who did not complete study time point t5 (3 days after LP) for any of these reasons will not be included in the final per-protocol analyses.

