### Sample size, randomization, and blinding

2.7

The sample size of N = 80 for the final analysis was chosen for reasons of feasibility while ensuring sufficient power to detect a clinically meaningful effect. With a power of 0.90, the study can detect an effect size f of at least 0.16 for the interaction effect between the group and time point on the primary outcome measure (headache-related impairment) (G*Power 3.1.9.7). This corresponds to a small to medium effect size. The recruitment period was set at 6 months (December 2023–May 2024), based on predetermined staff resources and estimates of the expected number of eligible study patients from recruitment from the wards. This timeline was expected to yield an effective sample size of 80 participants, accounting for an anticipated attrition rate of 15%.

Group allocation was performed after enrollment (i.e., after patients had provided written informed consent) via clustered block randomization, with a block consisting of 10 sequentially enrolled patients. To minimize the risk of communication between participants potentially influencing the outcomes, which can be a concern in settings like inpatient stays, the entire block was assigned to the same group. The sequence of all blocks was randomized before the start of the study based on a randomization list created in R. The last block of each group was truncated and ended as soon as the targeted sample size of n = 40 per group (not counting dropouts) was reached. The randomization list and the mode of randomization (clustered block randomization) were concealed from the blinded study assistant, who was responsible for recruiting and data collection, as well as from the clinical staff, to avoid unintended indirect influences from nurses or treating ward physicians. Only the study physician performing the ICP and LP according to the group allocation had the randomization list and was unblinded to group allocation.

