#### Main outcome: headache-related impairment

2.14.1

We hypothesize that headache-related impairment (main outcome) will be lower in the OPT group than in the SOC group during the main investigation period, assessed at three time points: 3 h (t3), 24 h (t4), and 72 h (t5) after LP. To test this hypothesis using a 2×3 mixed factorial study design, we will apply two-way repeated measures analysis of variance (ANOVA) to calculate an F-statistic on the main effect of the factor group (OPT vs. SOC) as well as the interaction effect between group and time point. The significance level (alpha level, type II error rate) for the probability over F (Pr(>F), *p*-value) will be set at 0.05. If *p* < 0.05, *post hoc* contrasts with correction for multiple comparisons (Bonferroni–Holm) will be performed. If the data do not meet assumptions of normality and homoscedasticity, we will instead use aligned rank transform ANOVA as the non-parametric alternative for the assessment of main effects and interactions (Wobbrock et al., 2011). The study will follow a per-protocol approach for the analysis.

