## Discussion

3

This study investigates the cumulative impact of several communication strategies designed to reduce nocebo-related headaches after lumbar puncture. Our objective is to apply knowledge derived from preclinical research on expectation effects and their modifiers, testing the efficacy of easily implementable techniques to diminish the nocebo component of procedure-related unwanted effects in a naturalistic clinical setting.

The nocebo effect is arguably more prevalent and impactful in clinical settings than its better-studied positive counterpart, the placebo effect. Patients’ experiences with healthcare are often dominated by negative emotions due to their association with illness and disease. Anxiety about health, fear, helplessness, and discomfort are common, especially in hospitals, where patients undergo diagnostic procedures that are unpleasant (Walker et al., 2021). This negative environment fosters nocebo effects, which are fueled by anxiety and negative emotions (Benson et al., 2023). The impact of nocebo effects is substantial, leading both to direct suffering from symptoms and indirect consequences such as patients refusing or discontinuing necessary diagnostic procedures or treatments due to fear of negative outcomes (Colloca and Miller, 2011).

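### The primary analysis keeps only patients who complete t5, so patients lost after the puncture are dropped together with their valid t3 and t4 ratings

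*Protocol article*

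**What the plan says.** Four sections of the protocol article set the rule together.

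- Section 2.5 lists reasons for ending participation after enrolment and then defines who is left out of the per-protocol set: "Patients who did not complete study time point t5 (3 days after LP) for any of these reasons will not be included". The reasons include "LP no longer indicated by medical personnel or the patient declined or aborted the procedure", a failed attempt, withdrawal of consent, and "significant deterioration in health, extended unavailability or incompliance of the patient for study participation".
- Section 2.14.1, on the main outcome, states "The study will follow a per-protocol approach for the analysis".
- Section 2.1 defines the 80 patients needed as "complete datasets from t1 to t5".
- Section 2.7 says the last block in each group "ended as soon as the targeted sample size of n = 40 per group (not counting dropouts) was reached", so dropouts are replaced.

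Section 2.7 also places allocation after study consent, and Figure 1 shows it before the informed consent talk, which is the intervention. Section 2.10.1 gives the primary outcome at 3 h, 24 h and 72 h. No analysis of all randomised patients, of all available ratings, or of sensitivity to the exclusions is described.

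**The concern.** This is a superiority comparison, and membership of its primary set depends on events after allocation. The exclusions fall into two groups with different consequences.

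**Lost after the puncture.** These patients may already have rated impairment at t3, or at t3 and t4. Section 2.12 allows t4 and t5 to be completed at home on the patient's own device and by telephone, so loss between t3 and t5 is a realistic route. The rule discards the ratings already given. If patients with more, or less, impairment are likelier to miss t5, the completers' means no longer represent the arms as randomised.

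**Lost at or before the puncture.** These patients have no post-puncture headache rating, so no primary data are thrown away. The question is whether the two consent talks lead to different numbers or kinds of patients proceeding. The Discussion itself lists among the consequences of nocebo effects "patients refusing or discontinuing necessary diagnostic procedures or treatments due to fear of negative outcomes", so the possibility lies within the authors' own theory.

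At stake is whether the main result can be read as the effect of the allocated communication.

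**Working it through.** **1. The plan's own figure.** Section 2.7 gives power 0.90 for f = 0.16 on the group-by-time interaction with N = 80. For the noncentral F test with k = 2 groups and m = 3 times, λ = f²·N·m/(1 − ρ), df1 = (k − 1)(m − 1) = 2 and df2 = (N − k)(m − 1) = 156. The correlation and sphericity are not stated; I assume ρ = 0.5 and ε = 1.

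- λ = 0.0256 × 80 × 3 / 0.5 = 12.29, which gives power 0.885.
- The smallest f detectable at power 0.90 is 0.164, which rounds to the stated 0.16.
- Over the assumed ρ, power runs from 0.75 (ρ = 0.3) to 0.99 (ρ = 0.7).

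The figure is reproduced, and it refers to 80 completers.

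**2. How many are excluded.** Attrition is 15% (section 2.7).

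- As a share of those randomised: 80 / 0.85 = 94.1, so 95 randomised and 15 excluded.
- As a simple mark-up: 80 × 1.15 = 92 randomised and 12 excluded.

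The protocol does not split this number into losses before and after the puncture.

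**3. What a given exclusion does to one arm's mean.** Mean in completers minus mean in all = −(share excluded) × (mean of excluded − mean of retained). The gap in points of the 0–10 scale is an assumption:

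| Share excluded | Gap 1 | Gap 2 | Gap 3 | Gap 4 |
|---|---|---|---|---|
| 5% | 0.05 | 0.10 | 0.15 | 0.20 |
| 15% | 0.15 | 0.30 | 0.45 | 0.60 |

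The values are shifts in one arm's mean, downwards if the excluded patients are the more impaired. The group difference changes only as far as the shifts differ between arms. The formula needs ratings to exist in principle, so it applies to patients lost after the puncture; the 15% row is therefore a ceiling.

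**4. Simulated example.** Assumptions: 47 patients per arm, ρ = 0.5, loss after t4 depending on the t3 and t4 ratings by the same rule in both arms, and about 14–15% loss in the control arm, all of it after the puncture.

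| True difference | Loss unrelated to impairment | Moderate dependence | Strong dependence |
|---|---|---|---|
| 0 | 0.00 | 0.00 | 0.00 |
| 0.30 SD | 0.30 | 0.28 | 0.26 |
| 0.50 SD | 0.50 | 0.47 | 0.44 |

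Entries are the mean differences among completers. At 0.50 SD, loss also becomes unequal: about 14–15% in the control arm against 10% (moderate) or 7% (strong) in the optimised arm. Under these assumptions the completer rule shrinks a real effect modestly and creates none where there is none.

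**5. Does the fix cost power?** If all 95 could be analysed, interaction power at f = 0.16 would be 0.934 and the detectable f 0.150, under the assumptions in step 1. This is an upper bound, because some of the 95 would have no puncture.

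**The case against.** The strongest reply is that most reasons in section 2.5 arise at or before the puncture: indication dropped, procedure declined or aborted, failed attempt, discharge beforehand, changed indication, staff unavailable. Those patients have no rating to discard, and an all-available-ratings set leaves them out just as the plan does. Patients who withdraw consent for data use cannot be kept either. Discharge after the puncture does not end follow-up, and a blinded assistant runs the surveys. All of this stands, and it confines the remedy by modelling to losses after t3.

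Three stronger readings are tempting, and the document does not support them.

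- *A sizeable false effect.* One can construct a 5-point artefact with no true effect. Take headache in 30% of both arms, with control patients missing t5 at 30% if they have headache and 10% if not, and loss unrelated to headache in the other arm. Control completers then show 0.3 × 0.7 / (0.3 × 0.7 + 0.7 × 0.9) = 25% against 30%. This makes post-puncture headache drive all loss in one arm and none in the other, and it uses incidence, a secondary outcome. If only 5% are lost after the puncture, with the same 3:1 ratio, the loss rates are 9.375% and 3.125%. The share is then 0.3 × 0.90625 / 0.95 = 28.6%, an artefact of 1.4 points.
- *The consent script is shown to cause refusals.* The Discussion speaks of nocebo effects in general and gives no rate for lumbar puncture.
- *The unblinded physician could steer logistical exclusions.* Nothing in the text shows this; the example given is unplanned unavailability of staff.

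**Conclusion.** The point holds in a limited form. The completer-only per-protocol set is a stated choice, repeated across sections, and not a detail left to an analysis plan. It conditions the primary comparison on events after allocation and discards valid t3 and t4 ratings from patients lost after the puncture.

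About 12 to 15 of some 92 to 95 randomised patients are excluded in total, if attrition is as planned. How many of them have ratings is unknown. Bias arises only if loss is related to impairment; its size and direction cannot be derived from the document, and the figures in the working are illustrations resting on assumed gaps and dropout rules. A reader might infer that the plan will favour the optimised arm. Nothing supports that: in the worked examples the estimate is either unchanged or moves against the trial's hypothesis. For patients never successfully punctured, the concern is possible selection by arm, to be shown by reporting because no analysis model can remove it.

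**What to change.** - **Primary set:** all randomised patients, by allocated arm, with a lumbar puncture performed and at least one rating at t3, t4 or t5, except those who withdrew consent for use of their data.
- **Primary model:** a mixed model with group, time and their interaction, using every available rating.
- **Sensitivity analysis:** the planned t5-completer ANOVA, or the aligned rank transform ANOVA where its assumptions fail.
- **Reporting:** declined, aborted and failed punctures and all other discontinuations, by arm and reason, so that selection before the puncture is visible.

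No new data are needed. Enrolment was set to end in May 2024, but the analysis is still described in the future tense. Power is not reduced. The costs are that the change must be declared as a deviation from the preregistered plan, and that the model relies on loss being missing at random given the observed ratings and on distributional assumptions for a 0–10 score that may contain many zeros. Keeping the rank-based completer analysis alongside helps to judge the distributional assumptions.

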#### Expectation of unwanted effects

2.11.1

As part of an assessment of procedure-related expectations using modified items of the Treatment Expectation Questionnaire (TEX-Q) (Shedden-Mora et al., 2023), the expectation regarding the extent of unwanted side effects after LP was rated on an NRS from 0 to 10 at t2 (immediately after ICP). The precise wording of the modified questions is provided in Supplementary Text S2.

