#### State anxiety

2.11.2

State anxiety was assessed immediately after ICP (t2) by calculating the total score from the 20 items of the state anxiety subscale from the State–Trait Anxiety Inventory (STAI) (Ferreira and Murray, 1983).

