#### Secondary outcomes

2.14.2

Current, mean, and maximum headache intensity will be tested using two-way repeated measures ANOVA or the non-parametric alternative, in alignment with the analysis of the main outcome. The headache incidence and the use of on-demand pain medication will be used to calculate odds ratios to compare the odds of developing headaches or using pain medication up until 72 h after LP between the OPT and SOC groups. Differences in expectations regarding the extent of unwanted side effects, state anxiety, perceived warmth and competence of the physician, and satisfaction with the procedure will be assessed using independent t-tests or Wilcoxon rank-sum tests (in the case of non-parametric data). For confirmatory analyses of group differences in the secondary outcomes, an alpha level of 0.05 after comparison for multiple testing using the Bonferroni–Holm procedure will be regarded as statistically significant.

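### The t5-completion rule also covers the outcomes measured at t2, so the expectation and state-anxiety comparisons drop patients who already have complete data for them

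*Protocol article*

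**What the plan says.** Section 2.5 lists events after enrolment that end participation. The first is "LP no longer indicated by medical personnel or the patient declined or aborted the procedure". Others are a failed puncture, withdrawal of consent to participation or to data use, medical or logistical barriers, and the later emergence of an exclusion criterion. The section ends with the rule that those who "did not complete study time point t5 (3 days after LP) for any of these reasons will not be included"; the exclusion is from the final per-protocol analyses. It exempts no outcome.

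Section 2.14.1 adds: "The study will follow a per-protocol approach for the analysis". Section 2.14.2 names no other set for the secondary outcomes. It plans t-tests or Wilcoxon rank-sum tests for "Differences in expectations regarding the extent of unwanted side effects, state anxiety, perceived warmth and competence of the physician, and satisfaction with the procedure", and treats the secondary group comparisons as confirmatory at 0.05 after Bonferroni–Holm.

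On timing, section 2.11.1 says that expectation "was rated on an NRS from 0 to 10 at t2 (immediately after ICP"), and section 2.11.2 says "State anxiety was assessed immediately after ICP (t2"). Figure 1 gives the order: consent talk, t2, puncture, then t3 to t5.

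**The concern.** A t2 outcome is complete once the t2 survey is done. A two-group test on it needs nothing that happens in the following three days. Section 2.1 ties complete t1–t5 datasets to the analysis of the main outcome only, so the article gives no reason to require t5 for a t2 outcome.

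The rule does more than waste data. Section 2.7 places allocation after enrolment and before the talk, so refusing the puncture after the talk is a post-randomisation event that the talk may influence. The Discussion itself says that fear of bad outcomes leads patients to refuse procedures. The rule can therefore remove from the anxiety comparison patients who left because they were anxious. These two outcomes test the first step of the proposed mechanism, from the talk to expectation and anxiety.

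**Working it through.** The article gives no figure for the t2 comparisons, so there is none to reproduce. The inputs taken from it are 80 completers (40 per group, sections 2.1 and 2.7) and 15% attrition (section 2.7). All other inputs are marked as assumptions.

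**1. How many t2 records are at stake**
- Enrolled patients needed: 80 / (1 − 0.15) = 94.1, so 95.
- Excluded: 95 − 80 = 15, about 7 per arm.
- The listed reasons run from enrolment. A cancelled indication, early discharge or unavailable staff can act before t2, and withdrawal of data use removes t2 data altogether. The article does not say how many excluded patients finished t2, so the range is 0 to about 15.

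**2. Precision, upper limit (all excluded patients have t2 data)**
- Ratio of standard errors: √(80/95) = 0.92, a reduction of about 8%.
- For an assumed difference of 0.5 SD, unadjusted two-sided 0.05 and independent patients, power by the noncentral t is 0.60 with 40 per arm and 0.67 with 47 per arm.

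**3. Bias when both arms are selected on anxiety**

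Assumptions: the t2 score is normal with SD 1, and the standard-of-care (SOC) mean is 0.5 above the optimized-communication (OPT) mean. A patient is excluded when a latent variable, correlated ρ with the t2 score, exceeds a threshold c that is the same in both arms. The mean among completers in an arm with mean μ is

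μ − ρ·φ(c − ρμ) / Φ(c − ρμ).

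Example with ρ = 0.5 and 15% excluded overall: c = 1.170. The completer means are 0.341 (SOC) and −0.114 (OPT), so the difference is 0.455 instead of 0.500.

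| Excluded overall | Difference, ρ = 0.5 | Difference, ρ = 0.8 |
|---|---|---|
| 5% | 0.48 | 0.44 |
| 10% | 0.46 | 0.41 |
| 15% | 0.46 | 0.39 |

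The loss is 0.02 to 0.11 SD. For scale, the standard error of the difference with 40 per arm is √(2/40) = 0.22 SD.

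**4. Bias when 15% are excluded in one arm only**
- Cut-off z = 1.036, φ(z) = 0.233; shift = ρ × 0.233 / 0.85 = ρ × 0.274.
- ρ = 0.5 gives 0.14 SD; ρ = 1 (exclusion wholly by anxiety) gives 0.27 SD.

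**5. Cross-check with a simpler model**

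Assume that refusers score 1 SD above their arm's mean. Removing a share q lowers that mean by q/(1 − q).
- 5% SOC against 0% OPT: 0.053 − 0 = 0.05 SD of an OPT benefit hidden.
- 10% against 2%: 0.111 − 0.020 = 0.09 SD.
- 15% against 5%: 0.176 − 0.053 = 0.12 SD.
- Equal shares with equal selection: 0.

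**The case against.** The strongest reply concerns scope. The per-protocol sentence stands under the main-outcome heading, section 2.1 links complete data to the main outcome, and a per-outcome analysis set is something an article may leave to the analysis plan. This does not remove the point. Section 2.5 states an exclusion rule for the final analyses, in the plural and without exemption, and section 2.14.1 makes the study its subject. A plan that used all patients with t2 data would have to depart from section 2.5 as written. The wider scope is nevertheless a reading of the text and is not spelled out for each outcome.

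Four stronger readings are tempting, and the article supports none of them.
- A reader might infer that every listed reason acts after t2. Several can act earlier.
- A reader might infer that 15% of usable t2 data are discarded. That is only the upper limit.
- A reader might infer that the bias is established. Many listed reasons are medical or logistical with no evident link to anxiety, no refusal rate is given, and the size rests on assumed correlations.
- A reader might infer that only a separate repair can reach the t2 tests. A general change of the analysis set to all allocated patients with available data would repair them too. A repair confined to the t3–t5 ratings would not.

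It is also true that a patient who refuses during the talk may never reach t2, so the fix recovers only some refusers. The two outcomes are secondary and described as supporting evidence, which limits the weight of the point.

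**Conclusion.** The point holds as a flaw in a stated rule. Followed as written, section 2.5 makes two confirmatory t2 comparisons depend on completing t5, which they do not need and which the talk may influence.

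The effect is modest and uncertain. Between 0 and about 15 patients with t2 data are lost, and the possible gain in standard error is at most about 8%. Bias is zero if exclusion is unrelated to the t2 scores, or if both arms lose the same share with the same selection. Under the assumptions above it is about 0.02 to 0.11 SD of a 0.5 SD difference, and 0.14 to 0.27 SD in the one-arm case. If standard communication causes more refusals among anxious patients, the bias runs toward no effect. A reader might infer that the rule would create a false benefit; the article gives no ground to expect that direction. The change is worth making because it costs little and uses data already collected.

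**What to change.** - In section 2.5, limit the t5-completion rule to the outcomes measured at t3 to t5.
- In section 2.14.2, analyse expectation of unwanted effects and state anxiety in all allocated patients with t2 data, in the group to which they were allocated, whether or not the puncture or t5 took place. Leave out only those who withdrew consent to data use.
- Reconcile the timing of warmth and competence, which is t2 in section 2.11.6 but t3 in Table 2 and section 2.12.5. If it is t2, the same set applies.
- Keep the t5-completer result as a sensitivity analysis.
- Report by arm the number of patients who declined before t2, since the new set cannot recover them.

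The cost is one sentence in each of the two sections, the timing correction and one reporting line, with no new data collection. The downside is that the denominators for the t2 outcomes will differ from 40 per arm and must be shown.
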